## Abstract

**Background:**

Rectal infection with *Chlamydia trachomatis* is one of the most common bacterial sexually transmissible infections among men who have sex with men (MSM) with diagnosis rates continuing to rise. Current treatment guidelines recommend either azithromycin 1 g single dose or doxycycline 100 mg twice daily for 7 days. However, there are increasing concerns about treatment failure with azithromycin. We are conducting the first randomised controlled trial (RCT) to compare treatment efficacy of azithromycin versus doxycycline for the treatment of rectal chlamydia in MSM.

**Methods/Design:**

The Rectal Treatment Study will recruit 700 MSM attending Australian sexual health clinics for the treatment of rectal chlamydia. Participants will be asked to provide rectal swabs and will be randomised to either azithromycin 1 g single dose or doxycycline 100 mg twice daily for 7 days. Participants will be asked to complete questionnaires about adverse drug reactions, sexual behaviour and drug adherence via short message service and online survey. The primary outcome is the treatment efficacy as determined by a negative chlamydia nucleic acid amplification test at 4 weeks post treatment. Secondary outcomes will utilise whole genome sequencing and mRNA assay to differentiate between treatment failure, reinfection or false positive results.

**Discussion:**

Rectal chlamydia is an increasing public health concern as use of pre-exposure prophylaxis against HIV becomes commonplace. Optimal, evidence-based treatment is critical to halting ongoing transmission. This study will provide the first RCT evidence comparing azithromycin and doxycycline for the treatment of rectal chlamydia. The results of this trial will establish which treatment is more efficacious and inform international management guidelines.

**Trial registration:**

Australian New Zealand Clinical Trials Registry ACTRN12614001125617.

## Background

Anogenital *Chlamydia trachomatis* is the most commonly diagnosed bacterial sexually transmissible infection (STI) with an estimated 131 million new cases of among 15–49 year-olds worldwide in 2012 [1]. In countries that screen both men and women for chlamydia, men account for approximately 40% of all new diagnoses [2–5]. Although these data do not differentiate between urethral, pharyngeal or rectal infection, available prevalence data among men who have sex with men (MSM) report that rectal infection (5.6–8.2%) is more common than urethral infection (2.1–5.4%) [6–9], with the L2b serovariant indicated in Lymphogranuloma venereum (LGV) [10].

The widespread uptake of biomedical prevention such as pre-exposure prophylaxis (PrEP) for HIV is likely to lead to further increases in rectal chlamydia among MSM [11]. Data from PrEP implementation studies in the US and Australia are showing an increased incidence of rectal STIs among MSM using PrEP [12–14]. The NSW PrEP Demonstration Project found an annual incidence of rectal chlamydia of 67.5% [14] with rates of between 33 and 48% observed in similar projects in the US [12, 13].

Current STI treatment guidelines recommend either azithromycin 1 g single dose or doxycycline 100 mg twice daily for 7 days for the treatment of rectal chlamydia [15–18]. However, there has been increasing concern about the effectiveness of azithromycin for rectal chlamydia with observational studies reporting failure rates of up to 22% [19–22].

In response to these concerns, guidelines in several countries are now recommending that rectal chlamydia infections are treated with 7 days doxycycline [15, 16, 18], rather than 1 g azithromycin as first line. However, there are potential problems adhering to a 7-day course of doxycycline which can lead to an increased risk of treatment failure [22].

A recent meta-analysis reported a treatment efficacy of approximately 83% for azithromycin 1 g single dose compared with 99% for doxycycline 100 mg twice daily for 7 days for rectal chlamydia infection [23]. However, this analysis was based on observational data only with no available evidence from randomized control trials (RCTs). Given that STI rates may continue to increase among MSM and that there is increasing concern about rectal chlamydia among women [24–26], treatment for rectal chlamydia must be proven to be efficacious. A double-blind RCT is urgently needed to rigorously estimate the difference in efficacy between azithromycin and doxycycline. The results will inform treatment guidelines worldwide.

### Research aim and hypothesis

The primary aim is to estimate the efficacy of azithromycin 1 g single dose for the treatment of rectal chlamydia among MSM and compare it to that of doxycycline 100 mg, twice daily for 7 days.

We hypothesize that doxycycline (100 mg, twice daily for 7 days) will be superior to azithromycin (1 g single dose) for the treatment of rectal chlamydia.

## Methods/Design

### Study design and setting

This is a double-blind (clinicians and patients) RCT. Given our primary outcome is treatment efficacy, our trial is double blind to minimize bias that could arise as a result of the different dosing regimens of the two drugs (7 days vs single dose). For example: i) it is possible that taking a 7-day course of daily doxycycline rather than a single dose of azithromycin may deter people from resuming sexual activity while taking treatment, thereby reducing their risk of a new infection, and; ii) participants could be less adherent to a 7-day regimen which could impact efficacy [27, 28]. The trial will be conducted within sexual health clinics in Victoria and New South Wales in Australia and in accordance with the Declaration of Helsinki. The trial was approved by the Alfred Hospital Ethics Committee (373/15).

*(NOTE: hereafter, “azithromycin” refers to azithromycin 1 g single dose and “doxycycline” refers to doxycycline (100 mg, twice daily for 7 days).*

### Duration of study

The trial will be of four weeks duration for each participant.

### Participant eligibility

#### Inclusion criteria

Men will be eligible for inclusion if they report male to male sexual contact in the past 12 months, are aged ≥16 years and test positive for rectal chlamydia using a nucleic acid amplification test (NAAT). They must have adequate English and comprehension skills to give informed consent.

HIV positive MSM will be eligible to participate as there is no evidence that treatment efficacy differs by HIV status. A recent RCT comparing azithromycin with doxycycline for the treatment of chlamydia urethritis found no difference in efficacy between HIV positive and negative men [29]. International STI management guidelines do not differentiate by HIV status for chlamydia treatment [15–18, 30].

#### Exclusion criteria

Men will be excluded if they: i) report use of antibiotics for other purposes in the last 2 weeks; ii) have a known contraindication to the use of azithromycin or doxycycline including allergy; iii) present with symptomatic proctitis. Because MSM will be recruited at clinical services, it will not be possible to genotype their infections to detect LGV at recruitment. LGV genotyping will take place at the conclusion of the trial. Men who are randomised and subsequently found to have asymptomatic LGV based on genotyping at the conclusion of the trial, estimated to be <6% of the trial population [31] will be excluded from our analysis as LGV requires more prolonged doxycycline treatment for cure [32]. The sample size will account for this – see *Sample Size*.

### Recruitment

MSM who are diagnosed with asymptomatic rectal chlamydia at participating clinics will be approached by a research nurse and invited to take part in the trial (Fig. 1). The nurse will explain the trial, assess eligibility and obtain consent. Eligible men will be enrolled and randomly assigned to either azithromycin or doxycycline. Participants will provide three self-collected rectal swab samples and complete a brief questionnaire. Self-collected swabs have been shown to have similar test performance compared with clinician-collected swabs for chlamydia testing [33]. Once randomly allocated to a treatment group, the nurse will then directly observe participants taking the first dose of treatment (with food).

**Fig. 1 Fig1:**
[figure not shown]
Outline of trial schema. Follow up at 4 weeks post recruitment

### Intervention

Participants will be randomly allocated to one of the following treatment groups:

Azithromycin: Participants will receive 1 g of active azithromycin (500 mg tablets × 2), plus 13 placebo doxycycline tablets, identical in appearance to the active azithromycin. Participants will be required to take the two azithromycin tablets under observation at time of recruitment and then advised to take a single placebo tablet morning and night for the next 7 days;

Doxycycline: Participants will receive 14 active doxycycline tablets (100 mg), plus one placebo azithromycin tablet, all identical in appearance to active azithromycin. Participants will be required to take one active doxycycline and one placebo azithromycin tablets under observation at time of recruitment and then advised to take a single active doxycycline tablet morning and night for the next 7 days.

Participants will be advised to take the drugs with food to minimize gastrointestinal side effects and to minimize sun exposure or use sun screen to reduce the risk of photosensitivity.

### Randomization and sequence generation, allocation concealment and blinding

A computer-generated randomization sequence will be created by an independent statistician. Blinded therapy will be prepared by an independent organization and labelled with individual kit numbers according to randomization. Study drugs will be packaged into individually numbered kits stored by independent site pharmacists. All tablets will be identical in appearance and feel, and all medications will be packaged identically to maintain blinding. Participants, physicians, nurses, trial statistician and all other trial staff will be masked to treatment group. The effectiveness of blinding will be tested at completion of the trial when participants will be asked to indicate which treatment they thought they received (including being able to indicate “don’t know”).

The side-effect profiles of the drugs will have negligible impact on blinding. They have been widely used for chlamydia for decades at the dosages we will be using. Their side-effect profiles are well established and similar including minor gastrointestinal upset (nausea, stomach cramps, diarrhoea, vomiting, gastric reflux) [34]. Photosensitivity may occur for doxycycline but is more common with longer or higher dosages [35]. Rash is a rare side effect for each drug, occurring in 0.1–1% of cases [34]. Our packaging will clearly state sunscreen should be used and exposure to sun minimalized, thereby reducing the risk of photosensitivity. We examined the side-effect data from treatment trials for urethral/cervical chlamydia and found that among 17 trials, there was no difference in side-effects (24.0% for azithromycin vs 23.0% for doxycycline, p = 0.45) [36].

### Outcomes

#### Primary outcome

Treatment efficacy measured as microbial cure defined as a negative chlamydia NAAT test result performed on a self-collected rectal swab at week 4.

#### Secondary outcomes

We will further differentiate between treatment failure and chlamydia re-infection using whole genome sequencing (WGS) and mRNA tests (see below for further detail) for any cases testing chlamydia NAAT positive on a rectal swab at week 4. Using the algorithm (Fig. 2), our secondary outcomes will be classified as: i) microbial cure based on a negative chlamydia NAAT test result at week 4; ii) false positive diagnosis if chlamydia NAAT positive at week 4, but no evidence of mRNA detected [37]; iii) new infection if infected with a different organism (based on sequencing results) OR if the same organism and the participant reports unprotected anal receptive sex between tests; iv) chlamydia treatment failure if infected with exactly the same organism and no reports of unprotected sex between recruitment and week 4 follow up. [NOTE: This algorithm assumes that if a man has a repeat infection with exactly the same organism confirmed by sequencing and reports unprotected sex, he will be classified as having a new infection rather than treatment failure. This is because unprotected sex is one of the greatest risk factors for chlamydia [38]. We acknowledge that this classification will not be 100% accurate, but this level of discrimination has never been previously undertaken in any study of chlamydia treatment efficacy. Our RCT design should ensure that cases classified as a new infection or a false positive diagnosis will be evenly distributed between trial arms, minimising any differential measurement bias.

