### Follow up

Men will be required to provide specimens and behavioral data until the conclusion of the trial at 4 weeks (Table 1). Men will be asked to attend the clinic at 4 weeks for a final study visit. At the 4-week visit, the research nurse will administer a final paper questionnaire and additional rectal swabs will be self-collected for WGS and mRNA assay.

**Table 1 Tab1:** Trial timeline

		Recruitment Day 1	Days 2-6	Day 7	Day 14	Day 21	Follow up Day 28
Recruitment							
Pre-eligibility assessment		X					
Informed consent obtained		X					
Enrollment and randomisation		X					
Dosage under supervision		X					
Data collection	Format						
Baseline questionnaire	Paper	X					
Adverse drug reactions	SMS/Online		X				
Sexual behaviour	SMS/Online			X	X	X	
Other medications	SMS/Online			X	X	X	
Drug adherence	SMS/Online			X			
Follow up questionnaire	Paper						X
Specimen collection	Number						
Self-collected swabs	3	X					
Self-collected swabs	2						X
Test of cure swab	1						X

*SMS* short message service. 3 swabs collected at recuitment: 1 for whole genome sequencing if required, one for mRNA and 1 for culture. 3 swabs collected at follow up: 1 for whole genome sequencing if required, 1 for mRNA and one for test of cure

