#### Weekly data collection

Participants will be asked to respond to a weekly short message service (SMS) that collects (via online link) whether they had: any receptive anal sex in the last week; sex with any new sexual partners; sex without a condom in the last week; used any douching and/or intra-rectal devices; any anogenital symptoms; any chlamydia testing elsewhere; taken any further antibiotics.

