#### At the 4-week follow up

Participants will complete another paper-based questionnaire that collects information regarding symptoms and sexual behaviour data, diagnosis of any STIs during follow up (which will be validated against their medical record) and what treatment they believe they received. We will also collect information about any recent HIV viral loads and/or CD4 counts.

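### For same-strain cases, new infection and treatment failure are defined by different exposures, and the SMS items as listed do not record the narrower one

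*Protocol article*

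**What the plan says.** The section Secondary outcomes classifies men who are NAAT-positive at week 4. Those without detectable mRNA are false positives, and those with a different organism are new infections. For the remaining men, who carry the same organism, three statements apply:

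- **Class iii, new infection:** "if the same organism and the participant reports unprotected anal receptive sex between tests".
- **Class iv, treatment failure:** "chlamydia treatment failure if infected with exactly the same organism and no reports of unprotected sex between recruitment and week 4 follow up".
- **Bracketed note:** a man with the same organism who "reports unprotected sex, he will be classified as having a new infection rather than treatment failure".

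The same section concedes imprecision: "We acknowledge that this classification will not be 100% accurate". It points to an algorithm in Fig. 2, which is not visible in the text at hand.

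Exposure is collected in two ways. Weekly data collection lists, as separate items, "any receptive anal sex in the last week; sex with any new sexual partners; sex without a condom in the last week". Table 1 places these messages at Days 7, 14 and 21. At Day 28, "Participants will complete another paper-based questionnaire that collects information regarding symptoms and sexual behaviour data". The individual questions of that form are not given.

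Secondary analysis then builds a binary per-protocol outcome in which new infections and false positives are pooled with cure and set against treatment failure.

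**The concern.** The binary secondary outcome needs every same-strain, mRNA-positive man to fall into exactly one class, because one side of the boundary counts as failure and the other as cure. The three statements do not draw the same boundary. Class iii turns on one specific act, class iv on any unprotected sex, and the note agrees with class iv rather than class iii. The period covered is also worded differently: class iii refers to the time between tests, class iv to the time from recruitment to week 4, and the note names no period.

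If this stays open, someone must decide which statement governs once sequencing results are known. That choice changes who counts as a treatment failure in the analysis meant to separate failure from reinfection, which the Discussion presents as a strength of the trial. The Discussion also relies on the SMS data to identify men at risk of reinfection, so it matters whether those data can support class iii.

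**Working it through.** The plan states no figure for this boundary, so the check is logical: apply each statement literally to every exposure pattern of a man who is NAAT-positive and mRNA-positive at week 4 with the same organism.

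**Step 1. Same window (recruitment to week 4) for all statements.** Two yes/no factors give 2 × 2 = 4 patterns.

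| Unprotected receptive anal sex | Other unprotected sex | Class iii met? | Class iv met? | Result from iii and iv | Note |
|---|---|---|---|---|---|
| no | no | no | yes | failure | failure (not sent to new infection) |
| no | yes | no | no | **neither** | **new infection** |
| yes | no | yes | no | new infection | new infection |
| yes | yes | yes | no | new infection | new infection |

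This gives 2 new infection, 1 failure, 1 neither and 0 both. The second row is the defect. Class iii does not accept the exposure, class iv rules the man out because of it, and the note calls him reinfected.

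**Step 2. Class iii window starting at the diagnostic NAAT.** Men are approached after diagnosis (Recruitment), so some time may pass between the diagnostic test and Day 1; its length is not given. Adding the same two factors for that period gives 2 × 2 × 2 × 2 = 16 patterns. Classes iii and iv then yield 10 new infection, 2 failure, 2 neither and 2 both. Both overlap patterns need unprotected receptive anal sex between diagnosis and recruitment and no unprotected sex afterwards. These are counts of patterns, not of patients. The gap appears under either reading of the window; the overlap appears only under the wider one.

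**Step 3. Can the listed SMS items supply the class iii exposure?** Class iii needs one act that is both receptive anal and condomless.

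- No to either item: the joint exposure is absent for that week.
- Yes to both items: undetermined. Receptive sex with a condom plus insertive sex without one gives the same answers as condomless receptive sex.

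The condomless-sex item does match the broader exposure in class iv and the note. The SMS items therefore fit two of the three statements and miss the third. The week after the Day 21 message can be covered only by the Day 28 questionnaire, and whether that form asks the joint question is not shown.

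**Step 4. Size.** The planning values give 280 × 0.07 = 19.6 and 280 × 0.02 = 5.6 NAAT-positive men per arm, about 25 in all (280 per arm being half of the effective 560). The document does not say how many would be mRNA-positive, same-strain and in the second row of the table. As a stress case only, assume that every positive starts as a failure and that 30% are reclassified (uncorrected chi-square, 280 per arm):

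| Failures, azithromycin vs doxycycline | p |
|---|---|
| 20 vs 6 (none moved) | 0.005 |
| 14 vs 4 (about 30% moved in each arm) | 0.017 |
| 14 vs 6 (30% moved in azithromycin only) | 0.069 |

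The result crosses 5% only when the shift is confined to one arm. The starting counts are too high, because false positives and different-strain infections leave first, and the per-protocol denominators would be below 280. These rows show only that the outcome rests on few events; they do not estimate the effect of the defect.

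**The case against.** The strongest defence is that the note already settles the matter. It places the man with only insertive or oral condomless sex, it makes class iv the complement of new infection, and under it the condomless-sex SMS item is sufficient. On that view class iii is just loosely worded. Fig. 2 may also show the branch clearly, and a condensed article need not print every questionnaire item. Much of this is fair. It does not remove the contradiction, because the note and class iii give different answers for the same man and the article does not say which governs. If Fig. 2 is clear, the text still has to match it. The concession about accuracy concerns imperfect discrimination, and the appeal to balance between arms does not say which class such a man belongs to.

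Four stronger readings are tempting but not supported:

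- **That the SMS measures neither exposure.** It lists condomless sex, which is the exposure in class iv and the note. Only the joint exposure is not listed.
- **That some men fit both classes.** This requires the class iii window to open at the diagnostic NAAT. The recruitment swabs listed under Table 1 include no NAAT, which makes that reading possible, but the baseline sequencing swab is taken at recruitment, so the same window as class iv is at least as natural.
- **That SMS non-responders become failures.** The words "exactly the same organism and no reports of unprotected sex between recruitment and week 4 follow up" could be read that way, but no such rule is stated. A man classified at week 4 has given a swab and is due to complete the questionnaire at that visit, and missing-data rules may sit in an analysis plan that is not shown.
- **That the conclusion would turn.** This rests on an assumed share and a one-sided shift. Trial staff and statistician are masked, and no mechanism for such a shift is evident.

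**Conclusion.** The definitions are inconsistent as written. Under any reading of the window, a same-strain, mRNA-positive man whose only condomless sex was not receptive anal sex meets neither class iii nor class iv. The note makes him a new infection, and hence cured in the second per-protocol analysis, on an exposure that class iii does not accept. The SMS items as listed cannot resolve class iii for a man who answers yes to both questions. The window wordings differ and should be aligned, but that is an ambiguity rather than a demonstrated overlap.

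The consequence is confined to this secondary outcome; the week 4 NAAT endpoint and its modified intention-to-treat analysis are untouched. The size cannot be derived from the document. The conclusion rests on the printed text, with Fig. 2 and the full questionnaires unseen. It is worth correcting because the boundary decides which of a small number of events count as failures, and because the correction is cheap.

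**What to change.** 1. Use one exposure, condomless receptive anal sex, and one window, first dose to the week 4 swab, in class iii, class iv, the note and Fig. 2. Word class iv as the exact complement: same organism, mRNA detected, exposure absent.
2. Ask the joint exposure as a single item in the weekly SMS, and again in the Day 28 questionnaire for the whole period since the first dose, so that the last week and any missed messages are covered.
3. Label same-strain cases with unknown exposure as undetermined, and analyse them once as failures and once as new infections in a sensitivity analysis.
4. Settle the wording before sequencing results are examined.

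Widening class iii to any unprotected sex would also remove the contradiction and needs no new item. It would, however, keep men with only insertive or oral exposure on the cured side.

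The cost is a short rewording and one question on two forms. Men recruited before the change may lack the joint item. For them, a no to either existing item rules out exposure for that week, and the Day 28 questionnaire may settle others. The rest become undetermined and enter the two-way analysis.

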#### mRNA

To ensure only actively transcribed nucleic acid is evaluated (as a marker of active, viable infection), extracted nucleic acid will be treated with 10U/μl DNase (Roche Diagnostic) for 10 min at 37 °C, followed by inactivation of DNase. Resultant RNA will undergo one-step reverse transcription and qPCR using the method by Storm et al. [37]. Any case that has mRNA detected will be classified as a true positive. Cases in which mRNA is not detected will be classified as false positive cases. Our trial will be the first to use mRNA assays to identify false positive cases.

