#### Secondary analysis

We will undertake two per protocol analyses in which participants who took less than 10 doses of their allocated treatment [28] or vomited within 1 h of any dose will be excluded: i) an analysis of the primary outcome of the microbial cure, and; ii) an analysis of the secondary outcome of microbial cure in which cases classified as new infection or a false diagnosis are grouped with microbial cure to create a binary variable for the analysis (microbial cure [including new infection and false positive cases] vs treatment failure).

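### If azithromycin fails more often, true failures relabelled as new infection will not be evenly spread between arms, and the risk difference in secondary per-protocol analysis (ii) shrinks

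*Protocol article*

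**What the plan says.** Secondary outcomes (Protocol article) sorts week-4 NAAT positives into categories. Category (ii) is "false positive diagnosis if chlamydia NAAT positive at week 4, but no evidence of mRNA detected". The mRNA section adds: "Any case that has mRNA detected will be classified as a true positive". A case that goes on to the split between new infection and failure therefore carries viable organism by the protocol's own criterion.

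Category (iii), new infection, covers a different organism, "OR if the same organism and the participant reports unprotected anal receptive sex between tests". Category (iv) is "chlamydia treatment failure if infected with exactly the same organism and no reports of unprotected sex between recruitment and week 4 follow up". The NOTE in the same section confirms that a man with a sequencing-confirmed identical organism who reports unprotected sex is not a failure: "he will be classified as having a new infection rather than treatment failure". The NOTE concedes that the classification is imperfect. It then relies on the randomised design, stating that "cases classified as a new infection or a false positive diagnosis will be evenly distributed between trial arms", and concludes that differential measurement bias is minimised.

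Under Secondary analysis, per-protocol analysis (ii) takes cases labelled new infection or false positive, which "are grouped with microbial cure to create a binary variable for the analysis", with treatment failure as the other level. The Analysis section reports the difference between proportions with a 95% confidence interval.

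**The concern.** The even-distribution sentence is the stated reason why the behaviour rule does no harm. It would be sound if the cases labelled new infection were all true reinfections. They are not. They also include true failures in men who happened to report unprotected sex, and the protocol's own hypothesis is that true failures are more common on azithromycin.

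At stake is the one planned analysis meant to isolate treatment failure from reinfection and false positives. If it moves more azithromycin than doxycycline failures into the cure group, it reports a smaller absolute difference with less power. A null or weak result could then be misread as showing that the excess of positives on azithromycin was reinfection.

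There is also a wording conflict. Category (iii) turns on unprotected receptive anal sex, while category (iv) and the NOTE turn on unprotected sex of any kind. A man with the same organism who reports only insertive unprotected sex meets neither (iii) nor (iv), yet the NOTE makes him a new infection.

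**Working it through.** **Inputs from the protocol (Sample size).** Planned cure is 98% on doxycycline and 93% on azithromycin, so non-cure is 2% and 7%. The effective sample is 700 × (1 − 0.14 − 0.06) = 560, or 280 per arm. Significance is 5%, taken as two-sided because that reproduces Table 2.

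**Assumed.** f is the true failure rate (same organism, viable). As an illustration, all planned non-cures are treated as true failures. q is the share of men with true failure who report unprotected sex before week 4. The protocol gives no value, so q is varied. It is set equal in both arms, as randomisation and blinding support.

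**Reproducing the plan.** The pooled-variance formula without continuity correction is

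n per arm = [1.960·√(2·p̄(1 − p̄)) + 0.842·√(p₁(1 − p₁) + p₂(1 − p₂))]² / (p₁ − p₂)².

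For 98% vs 93%, p̄ = 0.955. This gives (0.5746 + 0.2449)² / 0.0025 = 268.7, rounded up to 269 per arm or 538 in total, as in Table 2. Power at 280 per arm is 81.6% for 98% vs 93% and 90.5% for 98% vs 92%, in line with the stated 80% and 90%.

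**Applying the rule.**
- Failures relabelled per arm = 280 × f × q
- Recorded failure rate = f × (1 − q)
- Risk difference = (0.07 − 0.02) × (1 − q)
- Risk ratio = 0.07(1 − q) / [0.02(1 − q)] = 3.5 for every q below 1

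| q | Hidden, doxycycline | Hidden, azithromycin | Risk difference | Power |
|---|---|---|---|---|
| 0 | 0 | 0 | 5.0 points | 82% |
| 0.3 | 1.7 | 5.9 | 3.5 points | 66% |
| 0.5 | 2.8 | 9.8 | 2.5 points | 51% |
| 0.7 | 3.9 | 13.7 | 1.5 points | 34% |

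Example at q = 0.5: 280 × 0.02 × 0.5 = 2.8 and 280 × 0.07 × 0.5 = 9.8; recorded failure is 1.0% vs 3.5%. Whenever any failures are relabelled, the hidden count is 3.5 times larger on azithromycin.

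**Allowing for true reinfection.** Suppose 1 percentage point of each arm's positives is true reinfection, correctly labelled. True failure is then 1% vs 6%. At q = 0.5 the cases labelled new infection number 280 × (0.01 + 0.01 × 0.5) = 4.2 on doxycycline and 280 × (0.01 + 0.06 × 0.5) = 11.2 on azithromycin. The reinfection part balances (2.8 in each arm) but the total does not. The risk difference is again 2.5 points, with power about 62%.

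**At the meta-analysis rates.** The Background cites about 99% and 83% efficacy, so failure of 1% vs 17%. At q = 0.5 the rule hides 1.4 vs 23.8 failures and the difference falls from 16 to 8 points, though power stays above 99%.

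**The case against.** The strongest reply is that the rule was set in advance, reasoned, and accompanied by an admission that it is imperfect. Some same-organism infections after unprotected sex will be genuine reinfection, for instance from an untreated partner, and sequencing cannot separate these from failure. Per-protocol analysis (i) already counts every NAAT positive as non-cure, so the relabelled men are non-cures in one analysis and cures in the other. All of this stands, and it is a reason to keep the behaviour-based rule. But analysis (i) also counts different-organism reinfections and mRNA-negative positives as non-cure, so it does not isolate failure.

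A reader might infer several stronger points that the protocol does not support:

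- **That the misclassification is differential.** With equal q, a true failure has the same chance, 1 − q, of being recorded as failure in each arm. The counts are unequal but the error probabilities are not. The protocol's remark about minimising differential bias survives on that footing; the even-distribution claim does not.
- **That the efficacy estimate in the primary aim is inflated.** The primary outcome is a negative NAAT at week 4, analysed by modified intention to treat. No sequencing, mRNA or behavioural data enter that definition.
- **That receptive unprotected sex cannot be derived from the data.** The weekly message lists "any receptive anal sex in the last week; sex with any new sexual partners; sex without a condom in the last week" as topics, but the survey items are not shown. A negative answer on receptive sex or on sex without a condom already rules the exposure out for that week, and the week-4 questionnaire also collects sexual behaviour.
- **That failures are also lost through the false-positive category.** The protocol gives no sensitivity for the mRNA assay, so this cannot be sized.

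On the category conflict, the NOTE does place the man who reports only insertive sex, and the algorithm in Fig. 2 is not shown. What remains is inconsistent wording.

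**Conclusion.** The concern holds for secondary per-protocol analysis (ii) only. The statement that cases classified as new infection will be evenly distributed is false if azithromycin fails more often, which is what the trial hypothesises. The consequence is a risk difference multiplied by (1 − q) and a loss of power, with the risk ratio unchanged.

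The sizes are illustrative. They depend on a q that the protocol does not give and on treating every planned non-cure as a true failure. The powers are approximate: the protocol claims none for this analysis, the per-protocol set will be smaller than 280 per arm, and the expected doxycycline failures are few (280 × 0.01 = 2.8 at q = 0.5), so the normal approximation is rough. The direction for the risk difference needs only a higher failure rate on azithromycin, equal q in both arms, and some true failures among men who report unprotected sex.

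This does not threaten the trial's main result. It is a wrong justification, an attenuated secondary contrast and an inconsistent exposure definition. All three are worth correcting before the sequencing and mRNA results are classified.

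**What to change.** 1. Keep the behaviour-based rule and pre-specify a laboratory-only analysis beside it: same organism by WGS with mRNA detected is treatment failure, whatever sex is reported. Present the two as bounds on how these men are handled. The laboratory-only rule counts same-strain reinfection from an untreated partner as failure, which is why neither should stand alone.
2. Replace the even-distribution sentence with a statement that true reinfections should balance between arms, but that failures relabelled as new infection will not if the drugs differ, and that this attenuates the risk difference.
3. Use one exposure definition in (iii), (iv), the NOTE and the algorithm figure, so that the two same-organism categories are complementary.

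The cost is protocol or analysis-plan wording and one further tabulation from data already planned. No new specimens or visits are needed.
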